**Chapter 1**

**Background and Purpose**

**1.1 Objectives**

This study is a randomized clinical study with the following objectives:

- To determine the efficacy of phacoemulsification combined with intraocular lens (IOL) implantation by (1) the traditional procedure or (2) our new technique—IOL shell procedure in hard nucleus cataract surgery.
- To determine whether patients with hard nucleus cataract have less surgical complications following cataract surgery by (1) the traditional procedure or (2) our new technique-- IOL shell procedure.

**1.2 Rationale of the Study**

The study is conducted for the following reasons:

- Patients with hard cataract are very common in developing country. However, the application of phacoemulsification in these cases has been hindered by two surgical technical problems:

(1)There is few effective prevention methods for posterior capsular, traditional phacoemulsification techniques in hard nucleus cataract have serious surgical complications such as posterior capsular rupture and fragment dropping in vitreous cavity.

(2) It has been reported that Chinese have significant less anterior chamber depth than Caucasian. In order to avoid the posterior capsule rupture, traditionally, when emulsifying the last piece of fragment, the surgeon will intentionally elevate the nucleus to the anterior chamber, closer to the cornea, which increase damage on the corneal endothelial cells, leading to serious corneal edema.

- In this study, the IOL-shell technique allowed the surgeon to emulsify the last piece of fragment more posterior and comfortably in the bag with no need to worry the rupture of posterior capsule by the tip. Meanwhile, the increased distance between the phaco tip and endothelium provides more space that helps minimize the corneal endothelial damage.
- The advantage of our new technique may become more meaningful particularly in the eyes with endothelial dysfunction or shallow anterior chamber.
- The IOL act as a scaffold in our study provides a possible solution to above-mentioned problems.

**1.3 Summary of Study Protocol**

**Major eligibility criteria:**

- Cataract grade is severe than Grade 4.
- No other eye diseases except cataract.
- Pupil dilation >= 7 mm at the time of preoperative examination.
- Transparent central cornea, and a preoperative central endothelial cell count of >= 1500 cells per square millimeter.

**Treatment groups:** Eligible patients underwent one of two surgical techniques for cataract extraction: a new technique (the IOL was implanted in the capsular bag before the last nuclear fragment was removed) or the traditional technique (the IOL was implanted in the capsular bag after all nuclear fragments were removed).

**Examination Schedule:** The un-corrected visual acuity (UCVA) was recorded, using an ETDRS chart preoperatively at postoperative day 1, 7 and 30. The maximal incision thickness and central corneal thickness were recorded by anterior segment optical coherence tomography preoperatively and at each postoperative visit. Central corneal endothelial cell density was recorded preoperatively and at postoperative 7 and 30 day by non-contact specular microscopy. Central corneal endothelial cell loss was calculated on the basis of preoperative and postoperative endothelial cell density.

**Primary Outcome**: Endothelial cell loss, changes of central and temporal corneal thickness

**Secondary Outcomes:** Visual function, the mean ultrasound time (UST), US total equivalent power in position 3 (US power), the mean cumulative dissipated energy (CDE) and total BSS volume (V_BSS_), incidence of posterior capsular rupture and other ocular complications.

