**Chapter 4**

**Follow-up and evaluation of surgical outcomes**

**4.1 Follow-up Examination Schedule**

The frequency of follow-up examinations will approximate that practiced in standard clinical care, but may take place more frequently if there are complications. At a minimum, the patient will be examined 1day, 7 days, and 30 days following cataract surgery.

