**4.2 Follow-up Examination Procedures**

Principal safety outcomes include four measurements: central corneal endothelial cell loss, central cornea thickness, temporal corneal incision thickness and posterior capsular rupture.

Intraoperative outcomes include five measurements: ultrasound time (UST), US total equivalent power in position 3 (US power), cumulative dissipated energy (CDE), total BSS volume (V_BSS_), and surgical complications, recorded at the end of each surgery.

Postoperative outcomes include four measurements: (1) The un-corrected visual acuity (UCVA) was recorded by an ETDRS chart preoperatively at postoperative day 1, 7 and 30. (2) The maximal incision thickness and (3) central corneal thickness were recorded by anterior segment optical coherence tomography preoperatively and at each postoperative visit. (4) Central corneal endothelial cell density was recorded preoperatively and at postoperative 7 and 30 day by non-contact specular microscopy.

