**Chapter 5**

**Statistical Analyses**

The SPSS software package (version 17.0, SPSS Inc, Chicago, IL, USA) was used for statistical analysis. Changes of central corneal thickness and changes of temporal corneal incision thickness were compared using repeated measures ANOVA. Mean central cornea endothelial cell loss, UST, US power, CDE, and total BSS volume of the two groups were compared using a t test. Pearson’s chi-squared test was used for comparing gender, nucleus grade, Fisher’s exact test was used for preoperative UCVA and Mann-Whitney test was used for postoperative UCVA. Changes in outcomes were compared between treatments using a mixed effects model with covariate adjustment for baseline outcome. Mean changes and 95%CI derived from the mixed models are presented. All statistical tests were two-tailed with α= 0.05. A p value of < 0.05 was considered statistically significant.

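### Three unranked primary outcomes are each tested at 0.05 with no success rule and no deciding day for cell loss, so if any one result counts as success the chance of a false primary claim is about 8% to 19%

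*Protocol*

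**What the plan says.** Section 1.3 of the Protocol lists, under a singular primary-outcome label, "Endothelial cell loss, changes of central and temporal corneal thickness". It attaches no order, deciding visit or success rule to the three.

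The measurements are repeated. For cell loss, section 4.2 states that "Central corneal endothelial cell density was recorded preoperatively and at postoperative 7 and 30 day by non-contact specular microscopy". For the thicknesses, section 1.3 has the incision and "central corneal thickness were recorded by anterior segment optical coherence tomography preoperatively and at each postoperative visit". Section 4.1 sets the visits: "At a minimum, the patient will be examined 1day, 7 days, and 30 days following cataract surgery".

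Chapter 5 assigns the tests. For the thickness outcomes: "Changes of central corneal thickness and changes of temporal corneal incision thickness were compared using repeated measures ANOVA". Cell loss is compared between groups by a t test, with no day given. A baseline-adjusted mixed effects model for changes in outcomes is then added, without saying whether it is the main or a supporting analysis. The threshold is the same for every test: "All statistical tests were two-tailed with α= 0.05. A p value of < 0.05 was considered statistically significant". Primary and secondary outcomes are not distinguished.

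**The concern.** A primary outcome should tell the reader before the data are seen which result decides the trial. Here three results could do so, and one of them can be read at either of two days. The only decision rule in the document is a per-test threshold. It leaves open whether the claim that the new technique spares the cornea needs one significant outcome, a majority, or all three.

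If one is enough, each test has its own 5% chance of a false positive and the chances accumulate. The outcome and the cell-loss day that carry the claim could also be settled after the results are known. This affects the main benefit for which section 1.2 argues.

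**Working it through.** **Inputs from the Protocol**

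- Primary outcomes: 3 (section 1.3).
- Level of each test: 0.05, two-sided (Chapter 5).
- Cell loss: one t test per day, days 7 and 30 available, day not named. This gives 1 or 2 tests (section 4.2, Chapter 5).
- Central and temporal thickness: repeated measures ANOVA, which can give one between-group test per outcome across days 1, 7 and 30. This gives 2 tests (Chapter 5, section 4.1).

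**Input not in the Protocol**

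- Correlation between the test statistics: assumed equal for all pairs and varied from 0 to 0.9.

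Sample size, power and standard deviations are not given and are not needed here.

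**The plan's own figure.** The 0.05 is a design input for a single test: 1 − 0.95 = 0.05. The protocol states no trial-wide rate, so there is nothing further to reproduce.

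**Number of tests.** Cell loss at one day plus two thickness tests: 1 + 2 = 3. Cell loss at both days plus two thickness tests: 2 + 2 = 4. The extra mixed model is left out of the count because the protocol does not say what role it has.

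**Chance of at least one false positive, independent tests:** 1 − (1 − 0.05)^k.

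- k = 3: 1 − 0.95^3 = 1 − 0.8574 = 0.1426, or 14.3%.
- k = 4: 1 − 0.95^4 = 1 − 0.8145 = 0.1855, or 18.5%.

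**Correlated tests.** For k normal test statistics with common correlation ρ and critical value c = 1.96, the rate is

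1 − ∫ [Φ((c − √ρ z)/√(1−ρ)) − Φ((−c − √ρ z)/√(1−ρ))]^k φ(z) dz.

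Numerical integration gives the values below. Simulation with 500,000 draws per setting agrees to within about 0.1 percentage point.

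| Assumed correlation | 3 tests | 4 tests |
|---|---|---|
| 0 | 14.3% | 18.5% |
| 0.3 | 13.6% | 17.4% |
| 0.5 | 12.5% | 15.6% |
| 0.7 | 10.9% | 13.0% |
| 0.8 | 9.8% | 11.4% |
| 0.9 | 8.4% | 9.4% |

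**After repair**

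- One primary outcome at one visit: 5.0%. A fixed sequence after it stays at or below 5%, because each later test is made only if the one before it succeeds.
- Holm over three: the first step is at 0.05/3 = 0.0167. When no outcome has a true effect, an error needs at least one p-value below that step, so the rate is 1 − (1 − 0.05/3)^3 = 4.9% if independent. The same integral with the adjusted critical value gives 4.8%, 4.5% and 3.5% at correlations 0.3, 0.5 and 0.8.
- All three required: the chance that all three tests reject cannot exceed the chance that any given one does. If at least one outcome has no true effect, the rate is therefore at most 5% without adjustment.

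**The case against.** The strongest reply is that the inflation depends on a success rule that the protocol never states. If all three outcomes had to be significant, there would be no inflation. This stands: the documents show an undefined rule, and the 8% to 19% applies only to the any-one reading. But the protocol does not state the all-three rule either, and its only criterion is a threshold met test by test.

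A second reply is that hierarchy and multiplicity are commonly left to a statistical analysis plan, which is not at hand. That is fair for the details of a procedure. However, this protocol has its own statistics chapter, which sets one threshold for every test, and its own definition of the primary outcome, which lists three. The point rests on those two statements. A later plan that adjusted the level would have to depart from the threshold stated here.

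A third reply concerns size. Section 1.2 links endothelial damage to corneal oedema, so cell loss and central thickness may be strongly correlated. This is reasonable and is why the range runs to 0.9. The rate is still above 8% there.

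Stronger readings are tempting but not supported:

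- A reader might count eight primary tests (2 + 3 + 3 visits), for which 1 − 0.95^8 = 33.7%. Chapter 5 names repeated measures ANOVA for both thicknesses and specifies no visit-by-visit thickness tests, so the text supports three or four.
- A reader might say that the trial breaks a 5% error rate that it promised. The 0.05 is the level of each test, and no trial-wide rate is claimed.
- A reader might argue that day 7 must be ruled out because oedema would spoil the endothelial images. The protocol says nothing about image quality at day 7.

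**Conclusion.** The point holds in a limited form. The protocol names three primary outcomes without rank, tests each at two-sided 0.05, leaves the cell-loss day open and does not say what counts as success. On the reading that any one significant primary result is enough, the familywise error is 14.3% (three tests) to 18.5% (four tests) under independence, falling to 8.4% and 9.4% at a correlation of 0.9. Every setting examined exceeds 5%.

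This rests on three assumptions: the any-one reading, one between-group test per thickness outcome, and equal correlations chosen for illustration. The documents do not settle the first and give no data on the third. Whichever success rule was intended, it needs to be written down, because the error rate of the primary claim cannot be stated without it.

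**What to change.** Amend section 1.3 and Chapter 5 in one of three ways:

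1. **Single primary.** Name one outcome at one visit, tested at two-sided 0.05. Central endothelial cell loss at day 30, the last scheduled visit, is one example. Test the two thickness outcomes after it in a stated order, each by one named contrast from the repeated measures or mixed model.
2. **Three primaries under Holm.** Keep all three, fix the cell-loss day and name one contrast per thickness outcome. Compare the ordered p-values with 0.05/3 = 0.0167, 0.05/2 = 0.025 and 0.05.
3. **All three required.** State that the primary claim needs all three at 0.05, again with the cell-loss day and the thickness contrasts fixed.

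Under any of these, report the other visits and outcomes as estimates with 95% confidence intervals. Which outcome and visit to choose is for the sponsor; error control does not depend on that choice, provided it is fixed before the data are seen.

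The cost is a few sentences and no new data. The small downside is that an unadjusted p < 0.05 on one thickness outcome alone could no longer carry the primary claim. Options 2 and 3 also ask more of the data than a single test at 0.05. How much power that costs cannot be worked out from this document, which gives no sample size.

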**Chapter 2**

**Patient Recruitment and Enrollment**

**2.1 Participant Recruitment**

Age-related cataract patients meeting with the eligibility criteria were enrolled for the study.

**2.2 Exclusion Criteria**

Patients will be excluded from the study if they meet any of the following criteria:

- Intraocular pressure >21 mmHg
- Previous intraocular surgery
- Presence of other ocular disease (e.g. abnormal lens zonules, keratitis, glaucoma)
- History of ocular trauma

**2.3 Examination Procedures**

Ophthalmic examination will assess:

1. Visual acuity measured by ETDRS chart
2. Slit-lamp examination/photography
3. Anterior segment optical coherence tomography
4. Non-contact specular microscopy
5. Pupil dilation and cataract degree evaluation
6. Non-contact tonometer

Surgical equipment parameters will assess:

1. Ultrasound time (UST)
2. US total equivalent power in position 3 (US power)
3. Cumulative dissipated energy (CDE)
4. Total BSS volume (V_BSS_)

**Chapter 3**

**Surgical Protocols**

**3.1 Treatment Groups**

Patients will be assigned to one of two treatments:

1. Traditional phacoemulsification technique: IOL was implanted in the capsular bag with the injector system after nucleus was completely removed.
2. New technique: IOL was implanted in the capsular bag before the last nuclear fragment was removed.

**3.2 Surgical Protocols**

Surgery will be performed by a single surgeon (the PI, [name]).

**3.2.1 Surgical Protocol in the Traditional technique Group**

- A 3.0-mm temporal clear corneal incision was created.
- 5.5-mm capsulorhexis was made.
- IOL was planted in the bag after all nucleuses were removed.

**3.2.2 Surgical Protocol in the new technique Group**

- A 3.0-mm temporal clear corneal incision was created.
- 5.5-mm capsulorhexis was made.
- IOL was planted in the bag before the last nuclear fragment was removed.
- The last fragment was removed by phacoemulsification.

**3.3 Postoperative Medical Therapy**

For all patients, the standard postoperative regimen will consist of topical therapy included 0.3% tobramycin and 0.1% dexamethasone eye drops (Tobradex, Alcon Laboratories) four times per day and 0.3% tobramycin and 0.1% dexamethasone eye ointment (Tobradex, Alcon Laboratories) every night for one month.

**Chapter 4**

**Follow-up and evaluation of surgical outcomes**

**4.1 Follow-up Examination Schedule**

The frequency of follow-up examinations will approximate that practiced in standard clinical care, but may take place more frequently if there are complications. At a minimum, the patient will be examined 1day, 7 days, and 30 days following cataract surgery.

**4.2 Follow-up Examination Procedures**

Principal safety outcomes include four measurements: central corneal endothelial cell loss, central cornea thickness, temporal corneal incision thickness and posterior capsular rupture.

Intraoperative outcomes include five measurements: ultrasound time (UST), US total equivalent power in position 3 (US power), cumulative dissipated energy (CDE), total BSS volume (V_BSS_), and surgical complications, recorded at the end of each surgery.

Postoperative outcomes include four measurements: (1) The un-corrected visual acuity (UCVA) was recorded by an ETDRS chart preoperatively at postoperative day 1, 7 and 30. (2) The maximal incision thickness and (3) central corneal thickness were recorded by anterior segment optical coherence tomography preoperatively and at each postoperative visit. (4) Central corneal endothelial cell density was recorded preoperatively and at postoperative 7 and 30 day by non-contact specular microscopy.

**Chapter 5**

**Statistical Analyses**

The SPSS software package (version 17.0, SPSS Inc, Chicago, IL, USA) was used for statistical analysis. Changes of central corneal thickness and changes of temporal corneal incision thickness were compared using repeated measures ANOVA. Mean central cornea endothelial cell loss, UST, US power, CDE, and total BSS volume of the two groups were compared using a t test. Pearson’s chi-squared test was used for comparing gender, nucleus grade, Fisher’s exact test was used for preoperative UCVA and Mann-Whitney test was used for postoperative UCVA. Changes in outcomes were compared between treatments using a mixed effects model with covariate adjustment for baseline outcome. Mean changes and 95%CI derived from the mixed models are presented. All statistical tests were two-tailed with α= 0.05. A p value of < 0.05 was considered statistically significant.

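### Chapter 5 gives the primary corneal outcomes two between-group analyses and does not say which p value decides

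*Protocol*

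**What the plan says.** Section 1.3 of the protocol names the primary outcomes as "Endothelial cell loss, changes of central and temporal corneal thickness", that is, three corneal measures. Each is a change from a preoperative value, and section 4.2 confirms that cell density and both thicknesses are measured before surgery.

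Chapter 5 then sets out the comparisons in this order:

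- Thickness: "Changes of central corneal thickness and changes of temporal corneal incision thickness were compared using repeated measures ANOVA".
- Cell loss, together with the intraoperative measures: "Mean central cornea endothelial cell loss, UST, US power, CDE, and total BSS volume of the two groups were compared using a t test".
- A further comparison that does not list its outcomes: "Changes in outcomes were compared between treatments using a mixed effects model with covariate adjustment for baseline outcome".
- The source of the reported estimates: "Mean changes and 95%CI derived from the mixed models are presented".
- One rule for everything: "All statistical tests were two-tailed with α= 0.05", and "A p value of < 0.05 was considered statistically significant".

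No analysis in the chapter is called primary, confirmatory, supportive or sensitivity.

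**The concern.** On the plain reading, each primary outcome is compared between treatments twice: once by a test with no stated baseline covariate (t test or repeated measures ANOVA) and once by a baseline-adjusted mixed model. These are different tests and need not agree. The chapter says where the estimates and intervals come from, but not which p value gives the verdict.

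Two things are at stake. First, the report could quote a t test p value above 0.05 beside a mixed-model interval that excludes zero, or the reverse, and both would follow the protocol. Second, if the choice is left open until the results are known, the error rate for that outcome is no longer the stated 5%.

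**Working it through.** **Do the two sets overlap?** The mixed-model sentence concerns changes and adjusts for the baseline value of the outcome.

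- Ultrasound time, ultrasound power, CDE and BSS volume are recorded once, at surgery. They have no baseline and cannot be meant.
- The three primary outcomes are all changes with a preoperative value.
- Uncorrected visual acuity also has a preoperative value, but it has tests of its own (Fisher's exact test before surgery, Mann-Whitney after).

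The plain reading therefore includes the three primary outcomes. This is an inference, because the sentence lists none.

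**Is there a figure to reproduce?** No. The protocol states no sample size, power, effect or standard deviation. The only stated figure is the two-sided level of 0.05.

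**Size for cell loss.** This compares a t test on absolute change with a baseline-adjusted test of the same change.

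Inputs:
- Two-sided α = 0.05 for each test (Chapter 5).
- Assumed: one follow-up time, equal variances before and after surgery, and pre-post correlation r. The protocol gives no r, so a range is shown.

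With unit variances, baseline X and follow-up Y:
- Var(Y − X) = 2(1 − r).
- Var(Y − rX) = 1 − r².
- Cov(Y − X, Y − rX) = 1 − r².
- Variance ratio, adjusted to unadjusted = (1 − r²) / [2(1 − r)] = (1 + r)/2.
- Correlation k of the two test statistics = √[(1 + r)/2].

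The chance under the null that at least one of the two tests has p < 0.05 comes from the bivariate normal distribution with correlation k and limits ±1.96.

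| r | k | Variance ratio | Either p < 0.05 | Simulated |
|---|---|---|---|---|
| 0.3 | 0.806 | 0.65 | 7.8% | 8.0% |
| 0.5 | 0.866 | 0.75 | 7.3% | 7.3% |
| 0.7 | 0.922 | 0.85 | 6.8% | 7.1% |

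The simulation used an assumed 60 patients per arm and 4,000 replicates. Its standard error is about √(0.07 × 0.93 / 4000) = 0.4 percentage points, so it agrees with the calculation.

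Two consequences follow:
- If e is the chance that either test is significant, the two tests give opposite verdicts under the null with probability 2e − 0.10. That is 2 × 0.0681 − 0.10 = 3.6% at r = 0.7 and 2 × 0.0777 − 0.10 = 5.5% at r = 0.3.
- Baseline adjustment cuts the variance by 1 − (1 + r)/2, which is 15%, 25% and 35% at r = 0.7, 0.5 and 0.3.

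**Thickness outcomes.** The calculation above does not model repeated measures ANOVA against a mixed model, so no error rate is derived for them.

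**Three primary outcomes.** With one test each, and if independent, the chance of at least one false positive is 1 − 0.95³ = 14.3%. This arises even when each outcome has only one test.

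**The case against.** The strongest reply is the sentence "Mean changes and 95%CI derived from the mixed models are presented". Estimates and intervals come from one named analysis, and at a two-sided 5% level a 95% interval for a treatment difference is itself a test. A reader might infer that the mixed model is already the main analysis and that only a label is missing, which a statistical analysis plan could supply. Part of this stands: the sentence narrows the ambiguity and points to the natural resolution. It does not remove the ambiguity, because it is silent on the p value and leaves the t test and ANOVA without a role under the same significance rule. The protocol itself fixes both comparisons, so this is not a detail merely left to a later document.

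Several stronger readings are tempting, and the document does not support them:

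- *The either-test rate applies to all three outcomes and gives about 19% to 22% overall.* Only cell loss has a t test, and most of such a total is the 14.3% that comes from having three primary outcomes. Independence is also doubtful for corneal measures in the same eye.
- *The t test ignores baseline.* Section 1.3 calculates loss from preoperative and postoperative density. What is missing is covariate adjustment. Section 1.3 also does not say whether loss is absolute or a percentage, and the variance figures assume absolute change.
- *ANOVA averages over visits and so dilutes an early effect.* Chapter 5 does not say whether the group effect or the group-by-time term is the test.
- *Complicated eyes carry extra weight in the mixed model.* Section 4.1 says that visits "may take place more frequently if there are complications", but nothing says that unscheduled visits enter the model.
- *The analysis was chosen by its result.* Nothing in the protocol shows this. The point is only that the text would allow it.

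**Conclusion.** The point holds in a limited form. Chapter 5 commits to two between-group analyses of the primary outcomes, on the plain reading of an unlisted set of changes, and does not name the one that decides. For cell loss, a free choice between the two raises the error from 5% to about 6.8% to 7.8%. This rests on assumed correlations of 0.7 to 0.3, equal variances, absolute change and a single follow-up time. It shows scale and is not a property of this trial's data. For the two thickness outcomes the same ambiguity exists, but its size is not derived. The inflation is modest. The firmer reason to act is that the protocol does not determine a single verdict for any primary outcome.

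**What to change.** In Chapter 5, state that the baseline-adjusted mixed model is the single deciding analysis for endothelial cell loss and for the changes in central and temporal corneal thickness, and that the p value and the 95% interval both come from it. State that it uses the scheduled visits: days 1, 7 and 30 for thickness, and days 7 and 30 for cell density. The sponsor should name the deciding visit or contrast for each outcome in advance.

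Delete the t test for cell loss and the repeated measures ANOVA, or label them supportive. Keep the t test for ultrasound time, ultrasound power, CDE and BSS volume, which have no baseline.

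The cost is wording only. The model is already planned and the baseline values are already collected. This change does not address multiplicity across the three primary outcomes, which needs its own decision.

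### Nucleus grade is tested for baseline imbalance but adjusted for in no outcome analysis, which gives up precision and leaves chance imbalance in hardness uncorrected

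*Protocol*

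**What the plan says.** Chapter 5 (Statistical Analyses) assigns a method to each variable.

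- **Nucleus grade:** "chi-squared test was used for comparing gender, nucleus grade". This is its only appearance in the analysis. Preoperative UCVA gets a Fisher test in the same sentence.
- **Cell loss and ultrasound and fluid measures:** "Mean central cornea endothelial cell loss, UST, US power, CDE, and total BSS volume of the two groups were compared using a t test".
- **Corneal thickness:** central thickness changes and "changes of temporal corneal incision thickness were compared using repeated measures ANOVA", with no covariate named.
- **Visual acuity after surgery:** "Mann-Whitney test was used for postoperative UCVA".
- **Adjusted analysis:** changes in outcomes are also compared in a "mixed effects model with covariate adjustment for baseline outcome". No other covariate is named.
- **Error rate:** "All statistical tests were two-tailed with α= 0.05".

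Section 1.3 gives the primary outcome as "Endothelial cell loss, changes of central and temporal corneal thickness", so cell loss, which goes to a t test, is primary. Section 2.3 lists "Pupil dilation and cataract degree evaluation" among the examinations, and Section 1.3 uses grade for eligibility, so grade is known before surgery. Section 3.1 describes assignment to two treatments and mentions no stratification by grade.

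**The concern.** A significance test on a baseline variable is of little use when the arms were formed at random. Any difference in grade between arms is then due to chance, so the null hypothesis is true by design. A non-significant result does not show that the arms are alike, and a significant one leads nowhere, because Chapter 5 names no step that depends on it.

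The better use of grade is as a covariate. The trial is about hard nuclei, and grade is the obvious preoperative variable for hardness. It matters most for ultrasound time, ultrasound power, CDE and BSS volume. These are measured during surgery and have no baseline value, so the one covariate that the plan names cannot apply to them.

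At stake are the width of the confidence intervals and how far a chance difference in hardness between arms can move a result. The trial's validity is not in question.

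**Working it through.** The protocol states no sample size, effect size, standard deviation or power, so there is no figure of its own to reproduce. What follows is an illustration, with its assumptions marked.

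**1. Where grade could enter**

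| Outcome | Stated method | Covariate named | Grade |
|---|---|---|---|
| Endothelial cell loss (primary) | t test | none | no |
| Central and temporal thickness change (primary) | repeated measures ANOVA | none | no |
| UST, US power, CDE, BSS volume | t test | none; no baseline exists | no |
| Postoperative UCVA | Mann-Whitney | none | no |
| Changes in outcomes | mixed model | baseline of the outcome | no |

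**2. Precision.** Let R² be the share of outcome variance that grade explains. Where baseline is already in the model, R² is the share of the variance that remains. Adjustment multiplies the standard error of the treatment effect by √(1 − R²). The equivalent gain in patients is 1/(1 − R²) − 1.

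To turn this into power, assume a standardised effect of 0.5, 80% power and equal arms; two-sided α of 0.05 is from Chapter 5. Without adjustment, n per arm = 2 × (1.960 + 0.842)² / 0.5² = 62.8, or 63. With adjustment, n is multiplied by 1 − R². Power at 63 per arm is Φ(0.5 × √(63/2) / √(1 − R²) − 1.960).

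| R² (assumed) | SE multiplier | Gain in patients | n per arm for 80% | Power at 63 per arm |
|---|---|---|---|---|
| 0 | 1.000 | 0% | 63 | 80% |
| 0.05 | 0.975 | 5% | 60 | 82% |
| 0.10 | 0.949 | 11% | 57 | 84% |
| 0.20 | 0.894 | 25% | 51 | 88% |
| 0.30 | 0.837 | 43% | 44 | 92% |

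The formula ignores the few degrees of freedom that grade uses up.

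**3. What the chi-squared test lets through.** Assume 63 per arm and two enrolled grades, with half the eyes in the harder one. The standard deviation of the between-arm difference in that share is √(2 × 0.5 × 0.5 / 63) = 0.089. A difference of 1.5 standard deviations is 1.5 × 0.089 = 0.134, about 13 percentage points, with p about 0.13. The test would call the arms balanced. If the harder grade shifts the outcome by 1 SD, the unadjusted group difference moves by about 0.13 SD.

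This can be tied to the R² range. With half the eyes in each grade, R² = 0.25 × b², where b is the grade effect in outcome SDs.
- R² = 0.05 gives b = √(0.05/0.25) = 0.45 and a shift of 0.134 × 0.45 = 0.06 SD.
- R² = 0.30 gives b = √(0.30/0.25) = 1.10 and a shift of 0.134 × 1.10 = 0.15 SD.

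**4. What the baseline tests produce.** Three baseline tests (gender, grade, preoperative UCVA) at 0.05, taken as independent, give at least one significant result with probability 1 − 0.95³ = 14% under perfect randomisation.

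**The case against.** The strongest reply is that unadjusted comparison of randomised arms is valid, and that covariates beyond baseline are an efficiency preference often left to the SAP. The first half stands in full. A reader might infer that omitting grade biases the treatment effect or inflates the type I error. It does neither: a chance imbalance affects a single realised trial, and the stated tests already allow for it on average. The second half does not remove the point. The protocol leaves no gap here, because it assigns an unadjusted test to each outcome and names the covariate of its one model. The suggestion improves on a stated method.

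Other limits also stand:

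- **How strongly grade matters is not documented.** A reader might take Section 1.2 to say that hardness causes the endothelial damage. It ties hard nuclei to capsular rupture and dropped fragments, and attributes endothelial damage to lifting the last piece towards the cornea. That grade predicts cell loss or ultrasound energy among enrolled eyes is plausible, but the protocol does not state it.
- **Entry is restricted.** Section 1.3 admits only cataract above Grade 4, which narrows the spread of grade. Testing grade between arms implies that more than one grade is enrolled, but there may be only two.
- **Preoperative UCVA may already be adjusted for.** It can enter the mixed model as the baseline of visual acuity, so it cannot be said to serve only as a baseline test.
- **No sample size is given,** so the argument cannot rest on the trial being small.
- **The Mann-Whitney test has no error term.** The variance argument applies to the t tests, the repeated measures ANOVA and the mixed model; it does not carry over to postoperative UCVA.

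**Conclusion.** The point holds as a matter of efficiency and robustness. The plan spends grade on a test that can inform no decision and leaves it out of every analysis where it could sharpen the answer. If grade explains 5% to 30% of outcome variance (beyond baseline where that applies), leaving it out forgoes the equivalent of about 5% to 43% more patients. The protocol supplies no value for that share, and the entry restriction suggests the lower part of the range, where the gain is modest: at 63 per arm, power goes from 80% to 82% when R² is 0.05. The change is worth making because it costs so little, and because the ultrasound and fluid measures have no other covariate in the plan.

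**What to change.** Change Chapter 5 in three places:

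1. Report gender, nucleus grade and preoperative UCVA by arm descriptively, and drop the significance tests on them.
2. Replace the t tests on UST, US power, CDE and BSS volume by linear models with treatment and preoperative nucleus grade.
3. Analyse endothelial cell loss, central corneal thickness change and incision thickness change in models with treatment, the baseline value and nucleus grade. State that these are the analyses that count, in place of the unadjusted t test and the repeated measures ANOVA. Cell loss must be named explicitly. If grade is added to the mixed model alone, the unadjusted t test on this primary outcome still stands.

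The cost is a few sentences and a few degrees of freedom. Grade is already assessed before surgery, so no new data are needed and no clinical procedure changes.
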